# Rationale and design of the RIACT–study: a multi-center placebo controlled double blind study to test the efficacy of RItuximab in Acute Cellular tubulointerstitial rejection with B-cell infiltrates in renal Transplant patients: study protocol for a randomized controlled trial

**DOI:** 10.1186/1745-6215-13-199

**Published:** 2012-10-26

**Keywords:** Cellular kidney allograft rejection, B-cells, Rituximab

## Abstract

**Background:**

Acute kidney allograft rejection is a major cause for declining graft function and has a negative impact on the long-term graft survival. The majority (90%) of acute rejections are T-cell mediated and, therefore, the anti-rejection therapy targets T-cell-mediated mechanisms of the rejection process. However, there is increasing evidence that intragraft B-cells are also important in the T-cell-mediated rejections. First, a significant proportion of patients with acute T-cell-mediated rejection have B-cells present in the infiltrates. Second, the outcome of these patients is inferior, which has been related to an inferior response to the conventional anti-rejection therapy. Third, treatment of these patients with an anti-CD20 antibody (rituximab) improves the allograft outcome as reported in single case observations and in one small study. Despite the promise of these observations, solid evidence is required before incorporating this treatment option into a general treatment recommendation.

**Methods/Design:**

The RIACT study is designed as a randomized, double-blind, placebo-controlled, parallel group multicenter Phase III study. The study examines whether rituximab, in addition to the standard treatment with steroid-boli, leads to an improved one-year kidney allograft function, compared to the standard treatment alone in patients with acute T-cell mediated tubulointerstitial rejection and significant B-cell infiltrates in their biopsies. A total of 180 patients will be recruited.

**Discussion:**

It is important to clarify the relevance of anti-B cell targeting in T-cell mediated rejection and answer the question whether this novel concept should be incorporated in the conventional anti-rejection therapy.

**Trial registration:**

Clinical trials gov. number: NCT01117662

## Background

High dose steroid therapy is standard-of-care for treating acute T-cell mediated rejection of renal allografts, along with intensified maintenance immunosuppressive therapy in some cases (KDIGO-Guidelines
[1]). Only a minority of patients (20%) appears to be non-responsive to this treatment and may require additional treatments, for example, anti-thymocyte globulins
[2]. The general perception is that successfully treated acute T-cell mediated rejections do not harm the graft significantly. Yet, in clinical experience not all patients will recover with full function after the anti-rejection treatment. Particularly late rejections, occurring later than six months after transplantation, may have detrimental effects on long-term renal function
[3,4]. Even if renal allograft function returns to baseline values after anti-rejection therapy this may reflect some degree of compensatory hyperfiltration and obscure the loss of nephrons and development of interstitial fibrosis and tubular atrophy (IF/TA)
[5]. In fact, several studies have established a relationship between progressive IF/TA and T-cell mediated acute rejection even in subclinical rejection cases (that is, without significant impairment of the glomerular filtration rate at the time of rejection diagnosis)
[6,7].

Given these facts, the current treatment of acute T-cell mediated rejection may be suboptimal in many cases. One possible explanation could be that this type of rejection is more complex than reflected by current schemes and that therapy with steroids alone does not fully address this complexity. Recent studies demonstrated that more than 30% of the T-cell mediated tubulointerstitial rejections additionally contain a significant number of B-cells in the infiltrates
[8]. The actual pathogenetic role of these B-cell infiltrates remains to be established but the first studies and our own data indicate an inferior one-year allograft function and graft survival in patients with T-cell mediated rejections with B-cell infiltrates
[9-11]. Steroid therapy alone, which is primarily targeting T-cells, may not be adequate in these cases, raising the question of additional B-cell directed treatment strategies. Rituximab is a B-cell depleting antibody which is directed against the CD20 epitope and leads to apoptosis of mature B cells. It has been approved for treatment of diseases with B-cell activity, such as B cell lymphoma and rheumatoid arthritis
[12]. Thus far, only one pilot study examined the effect of rituximab in the treatment of biopsy-proven acute T-cell mediated rejection with B-cell infiltrates
[13]. In this randomized prospective study, 10 children with acute T-cell mediated rejection with B-cell infiltrates were treated with rituximab in addition to standard-of-care anti-rejection treatment (steroid boli and/or thymoglobuline). Compared with the control group of 10 children who received standard-of-care treatment only, rituximab-treated children had better recovery of allograft function (P = 0.026) and improved biopsy rejection scores (P <0.0001) at the follow-up biopsy after six months. Furthermore, a few case reports in adults suggest a benefit of rituximab alone or in combination with the usual anti-rejection treatment in patients with acute (therapy refractory) rejection
[14,15].

Beneficial effects of targeting B cells in T-cell-mediated acute rejection with rituximab can be based on the concept that allospecific T-cell/B-cell cross-talk in secondary lymphatic organs. After migration into the allograft and into nodular/tertiary lymphatic organs, B-cells induce an increased antigen presentation and aggravated chemokine milieu
[16]. This process may be halted by rituximab, as a single dose of rituximab at 375 mg/m^2^ has been shown to induce a sustained reduction of B-cells in the peripheral blood but also in the kidney allograft in most patients within the first 35 days
[17].

Despite the promise of the cited studies
[13,18] critical evaluation invariably leads to the conclusion that the evidence is not sufficient to treat acute transplant rejection with rituximab. This includes the small number of reported cases, short follow-up periods and heterogeneity of inclusion criteria, and the histological grading in these studies. Therefore, a double-blind, randomized, placebo-controlled trial with a sufficient number of patients and stringent histological defined inclusion criteria is needed.

These aspects are considered in the design of the RIACT-study. The acronym RIACT–study stands for a multi-center randomized placebo controlled double blind study to test the efficacy of RItuximab in Acute Cellular tubulointerstitial rejection with B-cell infiltrates in renal Transplant patients (RIACT).

## Design

### Study design

The RIACT-study is a randomized, double-blind, placebo-controlled, parallel group multicenter Phase III study. The study hypothesis is that treatment with rituximab in addition to the standard therapy with steroid-boli is superior to the standard therapy in acute T-cell mediated tubulointerstitial rejections in which B-cell infiltrates are present. The primary efficacy endpoint of the study is the change of the glomerular filtration rate (GFR) one year after intervention compared to the baseline GFR before the rejection episode.

Secondary endpoints are: 1) the progression of interstitial fibrosis and tubular atrophy (IF/TA) between the allograft biopsy that led to enrollment in the study and a scheduled protocol biopsy one year after intervention and 2) safety and side effect aspects of rituximab in kidney transplanted patients.

The study is recruiting a total of 180 patients with an acute T-cell mediated tubulointerstitial rejection who also show significant B-cell infiltrates in their biopsies, defined as >30 CD20+cells/hpf. After diagnosis of a B-cell-rich acute T-cell mediated tubulointerstitial rejection and informed consent (run-in phase), the patients will be centrally randomized for double-blinded treatment with rituximab or placebo, which will be given in addition to the standard anti-rejection therapy with steroid boli (study phase).

During the study phase a sufficient B-cell depletion (<5 B-cells/μl peripheral blood) after the first application of rituximab will be confirmed by fluorescence activated cell sorting (FACS) analysis. Patients with rituximab treatment and insufficient B-cell depletion undergo a second intervention with the same dose of rituximab. If a follow-up B-cell count in these patients reveals B-cells numbers above the target value, these patients will be excluded from the study. The follow-up period after intervention is 12 months. At this time, the primary endpoint renal allograft function change is determined, along with the secondary endpoints as safety parameters and degree of renal allograft fibrosis and tubular atrophy in a protocol biopsy.

The trial flow is outlined in Figure
1.

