Both treatment groups will receive additional medication that is intended to prevent potential side effects of rituximab, consisting of antihistaminics and an antipyretic medication (paracetamol) together with the study medication. All patients will also receive prophylaxis for pneumocystis jirovecii pneumonia for six months after the anti-rejection treatment according to the local center schemes.

According to the literature, a single dose of rituximab at 375 mg/m^2^ is able to induce a sustained reduction of B-cells in the peripheral blood but also in the renal allograft in most patients within the first six weeks
[17]. Following these findings and with the aim to keep the dosage of rituximab and, therefore, possible side effects as low as possible, rituximab will be given generally only once in the RIACT study. To assure a complete B-cell depletion in the peripheral blood (defined as <5 B-cells/μl), B-cell numbers in the peripheral blood will be assessed by FACS analysis on Day 35 ± 7.

Patients in the rituximab group with more than five B-cells/μl on Day 35 ± 7 will receive a second dose of rituximab (375 mg /m^2^). Accordingly, sufficient numbers of patients in the placebo group will be randomized in advance to receive a second round of placebo treatment. (For each patient in the placebo group it will be randomized in advance whether he will receive a second round of placebo treatment or not. If the rate of patients that need a second dose of rituximab is lower or higher than expected, the rate of patients that receive a second dose of placebo will be adapted.) In patients with a second treatment course, B-cells counts will be repeated on Day 72 ± 7. Patients in the verum group that continue to have more than five B-cells/μl in the peripheral blood will not receive further treatments with rituximab. Nevertheless, these non-responders will be followed at the regular study visits as well.

At the half-year visit after randomization (Day 182 ± 28), B-cell counts and laboratory tests will be repeated in all patients. One year after enrollment (Day 365 ± 28), final hematological and laboratory tests and a re-biopsy of the transplant will be performed (see Table
2). The progression of interstitial fibrosis and tubular atrophy ΔIF/TA between the biopsy that led to enrollment in the study and the biopsy one year after intervention will be quantified using specific staining und computerized image analysis.

**Table 2 T2:** Study visits

	

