### Methods against bias

The RIACT study is a double-blind, randomized, placebo-controlled phase III trial. Randomization will be performed centrally stratified by study center. The allocation to treatment arms results from a permuted-block randomization with variable block length. FACS results, that could give a hint which patient is in the verum respectively in the placebo group, will not be handed out to the study physician, but will be sent from the FACS facility to the unblinded randomization team in the Department of Biostatistics. The study physician will get the information concerning which patient has to receive a second dose of medication from the randomization team.

The biopsy readings, including quantification of fibrosis, will be done without knowledge of the assignment to the treatment groups. All biopsies will be submitted to a second reading by a panel of renal pathologists. Biopsies with divergent diagnoses will be discussed by the pathology consortium to reach a final diagnosis.

The primary analyses will be conducted on the intention-to-treat (ITT) population. Patients without complete B-cell depletion will also be observed and assessed according to the study protocol.

The likelihood of drop-outs from the study is negligible as all patients are under continuous surveillance in the participating centers. Although some patients may wish to withdraw prematurely from the trial, it is assumed that GFR-values one year after inclusion into the study - the primary endpoint of the study - can be obtained from all patients. However, if the GFR one year after inclusion into the study cannot be assessed, the last known plausible GFR value will be used, because it is assumed that a critical clinical progress will be carefully monitored.

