### Statistical analysis

The primary analyses will be performed in all patients who have received a least one dose of the study medication. Sensitivity analyses will be performed in the per protocol population, including all patients that finish the study at the last visit one year after study entry. The change in GFR between baseline and the assessment one year after the rejection episode will be performed with ANCOVA analysis adjusted for baseline, treatment and center. One interim analysis and one final analysis will be performed in this trial following the aforementioned decision rules (see Sample size calculation).

As soon as it can be demonstrated that rituximab is superior to placebo with respect to the primary endpoint, the secondary endpoint progression of interstitial fibrosis and tubular atrophy will be assessed in a confirmatory sense. Increase of fibrotic and atrophic interstitial area is analyzed with ANCOVA with treatment, center and baseline IF/TA in the first biopsy included as co-variates. Subanalyses will include the effect of rituximab in patients with different severity grades of rejection (Borderline, Type I and II), different immunosupression before inclusion in the study and patient groups receiving one versus two applications of rituximab. Frequency of adverse events will be reported per treatment group and analyzed with a chi-square test. *P*-values will be assessed descriptively.

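### The protocol contradicts itself on rituximab patients who stay above the B-cell target after a second dose: one section excludes them from the study, two others keep them

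*Protocol article*

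**What the plan says.** The protocol article deals with patients who fail B-cell depletion in three sections, and describes the primary analysis set in two.

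- **Study design.** The rule concerns the active arm: "Patients with rituximab treatment and insufficient B-cell depletion undergo a second intervention with the same dose of rituximab". It continues: "If a follow-up B-cell count in these patients reveals B-cells numbers above the target value, these patients will be excluded from the study".
- **Interventions and study plan.** After the repeat count at Day 72 ± 7, the rule for the same patients is this: "Patients in the verum group that continue to have more than five B-cells/μl in the peripheral blood will not receive further treatments with rituximab". The next sentence keeps them: "Nevertheless, these non-responders will be followed at the regular study visits as well".
- **Methods against bias.** "Patients without complete B-cell depletion will also be observed and assessed according to the study protocol". The sentence before it sets the analysis: "The primary analyses will be conducted on the intention-to-treat (ITT) population". If the one-year GFR cannot be assessed, "the last known plausible GFR value will be used".
- **Statistical analysis.** "The primary analyses will be performed in all patients who have received a least one dose of the study medication".

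Placebo patients receive a second round by advance randomization, not because of a B-cell count (Interventions and study plan). No section describes an exclusion of placebo patients on a B-cell count.

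**The concern.** A site or data manager reading Study design would take these patients out of the study. One reading the other two sections would keep them to one year. All of this is current text, so none of it is superseded wording, and the conflict is not a detail left to an analysis plan, because the article states both rules.

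The exclusion rule would matter if followed, for three reasons.

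1. **Comparability.** It depends on a response to the drug seen after randomization and has no placebo counterpart. The remaining rituximab patients would be a selected group set against an unselected placebo group.
2. **Blinding.** The protocol withholds FACS results from the study physician and gives some placebo patients a second infusion. A patient removed after the repeat count could only be a rituximab patient, so the removal itself would disclose the arm.
3. **Primary endpoint.** The one-year GFR of these patients would be left out or replaced by a value from the first weeks. They would also leave the per-protocol set, which requires completion of the one-year visit.

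**Working it through.** **1. The passages side by side**

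| Section | Patients concerned | What happens to them |
|---|---|---|
| Study design | Rituximab, above target after the second dose | Excluded from the study |
| Interventions and study plan | Rituximab, still above 5 B-cells/μl at the repeat count | No more rituximab; followed at regular visits |
| Methods against bias | Incomplete depletion | Observed and assessed; ITT primary analysis |
| Statistical analysis | Anyone given one dose or more | In the primary analysis |

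The first two rows name the same patients and give opposite instructions. The last two rows agree with the second. ITT and dosed-at-least-once are not identical sets, but that is a separate matter: a patient who has had two doses belongs to both.

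**2. The plan's own figure**

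Inputs from Sample size calculation: difference 12 ml/min, SD 27.8, two-sided 5%, power 80%.

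n per group = 2 × (1.960 + 0.842)² × 27.8² / 12² ≈ 84.3, which rounds up to 85. The exact t-test gives 86, as stated. The SD of 27.8 is therefore used below. The contradiction itself changes no stated number.

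**3. Illustration if the excluded patients were dropped from the analysis**

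Let f be the fraction of the rituximab arm removed, and g the amount by which their mean GFR change falls below that of the rest of the arm. If the rest have mean m, the whole arm has mean (1 − f)m + f(m − g) = m − fg. Removal therefore raises the arm mean by f × g.

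The documents give neither f nor g. Assumed ranges:

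- f = 3–10%, that is 0.03 × 90 = 2.7 to 0.10 × 90 = 9 patients.
- g = 10–14.5 ml/min. The upper end is the protocol's optimistic effect (2.5 − (−12) = 14.5). It corresponds to a non-depleted patient gaining nothing from rituximab.

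Shift:

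- Low end: 0.03 × 10 = 0.3 ml/min, or 0.3/12 = 2.5% of the conservative planned effect.
- High end: 0.10 × 14.5 = 1.45 ml/min, or 1.45/12 ≈ 12% of it.

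Effect on a nominal one-sided error of 0.025, ignoring the interim look and supposing no overall treatment effect: error = 1 − Φ(1.96 − fg/SE), with SE = 27.8 × √(1/(90(1 − f)) + 1/90).

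- f = 3%, g = 10: SE = 4.18, error = 1 − Φ(1.96 − 0.07) ≈ 0.030.
- f = 10%, g = 14.5: SE = 4.26, error = 1 − Φ(1.96 − 0.34) ≈ 0.053.

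**4. If their last value were carried forward instead**

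The patient stays in the analysis, so f × g does not apply. Table 2 lists assessment of allograft function at Visits 1, 5 and 6, and laboratory tests at Visits 4 and 4c. If those tests include creatinine, the carried value dates from about Day 35 or Day 72. It may lie above or below the one-year value, depending on whether function would later have declined or recovered. The direction cannot be fixed from the documents.

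**5. If the patients are kept, as the other sections say**

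This source of bias is zero and the 180 patients stand.

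**The case against.** The strongest reply is that the document mostly settles the question the safe way. The detailed procedural section addresses exactly these patients and retains them, Methods against bias repeats this, and neither account of the primary analysis makes depletion a condition. Against that stands one sentence in the design summary. This stands: retention looks like the intention, and harm arises only if the summary sentence is followed. It does not remove the contradiction.

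Several stronger readings are tempting but unsupported:

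- **That the plan is biased towards rituximab.** This needs the exclusion sentence to override the other sections. It also needs non-depleted patients to have worse GFR, which is plausible under the trial's rationale but nowhere stated. The protocol's term non-responder refers to B-cell counts, not graft function.
- **That the shift could be larger.** A deficit of 20 ml/min in 10% of the arm would give 2.0 ml/min, but 20 exceeds the whole planned effect of 12–14.5 ml/min.
- **That the primary endpoint would certainly be lost.** Methods against bias expects a one-year GFR even from patients who withdraw early, and gives a last-value rule otherwise. Omission and carry-forward are alternatives and cannot both be counted.
- **That the carried value would come from the rejection episode.** It could come from the Day 35 or Day 72 laboratory tests.
- **That power would suffer badly.** Losing 9 patients exceeds the reserve of two per group, but 81 against 90 patients with a difference of 12, SD 27.8 and the final one-sided threshold of 0.023 still gives fixed-sample power of about 79–80%, against about 82% with 90 per arm.

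**Conclusion.** The point holds as an internal contradiction. Study design excludes patients whom Interventions and study plan and Methods against bias retain, and whom both descriptions of the primary analysis include. The exclusion is wrong for a randomized comparison: it acts in one arm only, depends on a drug response after randomization, and could disclose allocation.

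The documents establish neither the size nor the direction of any bias. The range of about 0.3–1.5 ml/min in favour of rituximab is an illustration. It rests on three assumptions: the exclusion is applied, the patients are dropped from the analysis, and 3–10% of the arm is affected with a deficit no larger than the planned effect. Under carry-forward the distortion could go either way, and if the patients are retained there is none. The error rates shown also suppose that non-depleted patients do worse even when rituximab has no overall effect.

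**What to change.** Delete the exclusion sentence from Study design and reconcile that section with Interventions and study plan and Methods against bias. State in its place that patients without B-cell depletion remain in follow-up to the one-year GFR and biopsy, and are analysed in their assigned arm whatever their B-cell count.

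The change concerns follow-up and analysis only; the dosing rule is left as it is. It costs a one-sentence amendment and no extra visits, because the other sections already plan the follow-up. As the trial is recruiting, sites should be told promptly, since one-year data not collected after an exclusion may not be recoverable.
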